#### Performance of the Canadian C-Spine Rule (secondary study outcomes)

The rule will be evaluated during the run-in and evaluation periods for all enrolled cases with completed Paramedic Data Forms.

a) Accuracy of the rule, i.e. sensitivity and specificity for identifying clinically important cervical spine injuries.

b) Paramedic accuracy in overall interpretation of the rule (immobilization required versus no immobilization required) will be determined by comparing the paramedics' response on the data collection form to the 'gold standard' interpretation of the rule made by the Investigators' Steering Committee. Attention will be focused on fractures missed or potentially missed by paramedic misinterpretation.

c) Paramedic agreement and comfort with and use of the rule. Paramedics, on the data collection form, will be asked to indicate their comfort in following the rule for each specific patient, using a five-point Likert scale. If the paramedic decides not to follow the rule, they will be asked to indicate reasons for their decision and if they recommend that additional follow-up and clarification from the study champion would be helpful. Ongoing education at regular intervals is a feature of the intervention and it will be important to address paramedics' concerns about using the decision rule.

### Data analysis

#### Measures of safety

We will list the number and describe the details of any cases deemed to be missed cervical spine injury or adverse outcome after clearance by the paramedics. The percent of missed cervical spine injuries will be estimated with point and 95% confidence intervals [CIs]. The estimates will be compared between validation and evaluation periods although we expect the missed injury rate to be 0% in both cases.

#### Measures of clinical impact

a) Proportion of low-risk patients transported without immobilization will be described as overall proportion with 95% confidence intervals, based upon a denominator of patients actually assessed by participating paramedics as judged by the completion of a Paramedic Data Form. This will be compared to the immobilization rate in the validation study, which we know to be close to 100% since paramedics were required to immobilize all patients by protocol.

b) Lengths of time will be presented as means plus standard deviations. We will compare time intervals for those patients assessed as part of the evaluation phase of this study, to those assessed during the validation study at the Ottawa site using the Student's t-test.

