**Discussion:**

Approximately 40% of all very low-risk trauma patients could be transported safely, without c-spine immobilization, if paramedics were empowered to make clinical decisions using the Canadian C-Spine Rule. This safety study is an essential step before allowing all paramedics across Canada to selectively immobilize trauma victims before transport. Once safety and potential impact are established, we intend to implement a multi-centre study to study actual impact.

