### Study population

#### Inclusion Criteria

We will enroll consecutive alert, stable adults evaluated by the paramedics with potential c-spine injury after sustaining acute blunt trauma. These are patients for whom standard EMS protocols require immobilization. Patient eligibility will be determined at the time of paramedic arrival at the scene based on the following criteria:

a) "Potential c-spine injury after sustaining acute blunt trauma" will include patients with either: i) neck pain with any mechanism of injury (subjective complaint by the patient of any pain in the posterior aspect of the neck),

ii) no neck pain but some visible injury above the clavicles, and/or

iii) neither neck pain nor visible injury, but significant mechanism of injury as determined by the paramedic at the scene.

b) "Alert" is defined as a Glasgow Coma Scale [80] score of 15 (converses, fully oriented, and follows commands).

c) "Stable" refers to normal vital signs as defined by the Revised Trauma Score [7] (systolic blood pressure 90 mm Hg or greater and respiratory rate between 10 and 24 breaths per minute).

d) "Acute" refers to injury within the past 4 hours.

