### Outcome measures and data collection

#### Data collection

The following outcome data will be collected by dedicated study personnel who will review daily patient logs, ED patient records, diagnostic imaging reports, and in-patient records. All participating paramedics will complete a Paramedic Data Form at the time of each patient assessment as well as document patient care on their province wide Ambulance Call Reports. Additional study data will be recorded on a Case Record Form. All outcomes will be collected during the run-in and evaluation periods, but the run-in data will not be used in the final analysis (this run-in phase may be shortened if no issues are identified).

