#### Measures of clinical impact (primary study outcomes)

a) Proportion of low-risk patients transported without immobilization, i.e. proportion of eligible trauma patients who are not immobilized by paramedics. Daily EMS patient census logs will be reviewed to identify potential neck injury patients and then ED patient records (including ambulance call reports, nursing notes, and physician notes) will be assessed to determine eligibility. All eligible patients assessed by participating paramedics will be considered for the denominator of this measure. We will also report the number of eligible patients not assessed.

b) Lengths of time, i.e. time spent in the field before transport, time from ED arrival to transfer of patient care to ED staff; and total patient length of stay in the ED. These times will be compared, for those patients transported with and without spinal immobilization as part of the evaluation phase of this study, to those transported with immobilization (100% cases) during the validation study at the Ottawa site. We will only measure times for those patients who are assessed and enrolled by the paramedics.

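### The clearance proportion is defined on eligible patients but analysed only in those with a completed Paramedic Data Form, so it is likely, though not certain, to overstate the share of eligible patients spared immobilization

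*Protocol article*

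**What the plan says.** Three statements in the protocol article set the population for this outcome, each narrower than the last.

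- **Definition.** Under Measures of clinical impact (primary study outcomes), item a, the outcome is the "proportion of eligible trauma patients who are not immobilized by paramedics".
- **First restriction, same item.** "All eligible patients assessed by participating paramedics will be considered for the denominator of this measure." The item adds: "We will also report the number of eligible patients not assessed."
- **Second restriction.** Under Data analysis, Measures of clinical impact, item a, the proportion and its 95% confidence interval are "based upon a denominator of patients actually assessed by participating paramedics as judged by the completion of a Paramedic Data Form".

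Four other statements bear on it.

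- **How eligible patients are found.** The outcome item says: "Daily EMS patient census logs will be reviewed to identify potential neck injury patients". Eligibility is then settled from the ED records, which include the ambulance call reports.
- **Form instruction.** Data collection says: "All participating paramedics will complete a Paramedic Data Form at the time of each patient assessment".
- **Default care.** Inclusion Criteria says of the study population: "These are patients for whom standard EMS protocols require immobilization".
- **Planning figure.** Sample size anticipates clearance of up to 40% of assessed patients, with 3,000 enrolled, and says the results will inform the design and size of the Phase IV trial.

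**The concern.** The outcome is worded for eligible patients, but the analysis set depends on a document written by the same person who makes the immobilization decision. A paramedic who never starts an assessment and immobilizes by default owes no form. That patient is eligible and not spared immobilization, yet is absent from the denominator. Reasons for not following the rule are also recorded on the form, so complete non-use does not appear in the secondary outcome on use of the rule either.

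At stake is how the headline number is read. As clearance among patients in whom the rule was applied and documented, it is sound. As the share of eligible patients in the service who are spared immobilization, which is how the outcome is defined, it may be too high. The article says the result will feed the Phase IV design and that partner organizations intend to use the findings to change policy. Both uses call for the service-wide figure.

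**Working it through.** **The plan's own figure.** The article gives no formula, power or precision target for this outcome; the 3,000 rests on feasibility and investigator consensus, so there is no calculation to reproduce. The nearest check is the paramedic validation study, where 62.2% of recruited patients would have needed immobilization under the rule. 1 − 0.622 = 0.378, or 37.8%. This is 2.2 points below 40% and compatible with a figure stated as an upper expectation. Both are per assessed or recruited patient.

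**Inputs**

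- p = 0.40, the proportion not immobilized among patients with a form (Sample size).
- n = 3,000 (Sample size), taken here as the number with a form; 0.40 × 3,000 = 1,200 cleared.
- c = share of eligible patients with a completed form. Not in the document; assumed, shown as a range.
- q = proportion not immobilized among eligible patients without a form. Not in the document; assumed, shown as a range.

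**Formulas**

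- All-eligible proportion: P = c·p + (1 − c)·q.
- Difference between the form-based and all-eligible figures: p − P = (1 − c)(p − q). It is positive only when q < p, zero when q = p, and negative when q > p.

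**All-eligible proportion when the form-based figure is 40%**

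| Form capture c | q = 0% | q = 20% | q = 40% | q = 60% |
|---|---|---|---|---|
| 95% | 38% | 39% | 40% | 41% |
| 90% | 36% | 38% | 40% | 42% |
| 80% | 32% | 36% | 40% | 44% |
| 70% | 28% | 34% | 40% | 46% |
| 50% | 20% | 30% | 40% | 50% |

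At c = 80% and q = 20%, for example: 0.8 × 0.40 + 0.2 × 0.20 = 0.32 + 0.04 = 0.36.

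**Against sampling error.** The Wilson 95% interval is [p + z²/2n ± z√(p(1 − p)/n + z²/4n²)] / (1 + z²/n), with z = 1.96. For 1,200/3,000 it is 38.3% to 41.8%. With q = 0, P = 0.40c, which falls below the lower limit when c < 0.3826/0.40 = 0.957. So if no patient without a form is cleared, capture below about 96% puts the all-eligible figure outside the form-based interval. At 80% capture the eligible total is 3,000/0.8 = 3,750, and 1,200/3,750 = 32.0% (95% CI 30.5 to 33.5), a gap of 8 points.

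**If q is left free.** At 80% capture, q = 0 gives 0.32 and q = 1 gives 0.32 + 0.20 = 0.52. Knowing only how many eligible patients lack a form therefore bounds the all-eligible proportion between 32% and 52%.

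**The case against.** The case for leaving the plan alone has real weight.

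- **The restriction is declared.** The outcome item itself limits the denominator to assessed patients and promises a count of those not assessed. A reader can derive a worst-case figure from that count. This stands, but a count gives only bounds, not the immobilization status of those patients.
- **The form is required.** A reader might infer that completing it is optional. The document says otherwise: Data collection requires it at each assessment, and Ethical Considerations makes participation mandatory. Overrides are permitted and recorded on the form, so a patient immobilized against the rule stays in the denominator. Only patients with no form are lost.
- **The estimand suits the aim.** The article calls this an efficacy study and leaves effectiveness to a later trial. Clearance among assessed patients is a legitimate efficacy quantity and matches the basis of the 40% planning figure. Replacing it as the primary denominator would be a preference, not the correction of an error.
- **An all-eligible denominator has difficulties of its own.** It would take in patients attended by paramedics not yet trained or certified. Eligibility by mechanism alone depends on the attending paramedic's judgement and may not be fully recoverable from records.
- **The wording of the 40% is editorial.** A reader might take the abstract's sentence, "Approximately 40% of all very low-risk trauma patients could be transported safely", as a further denominator. The outcome item equates its low-risk patients with eligible trauma patients, and the article uses the very-low-risk phrase loosely for the population to whom the rule is applied. No planned analysis changes.

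What these points do not answer is that the definition and the analysis name different populations, and that no proportion is planned for the population in the definition.

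**Conclusion.** The point holds as a mismatch between definition and analysis, with a likely but unproven upward bias. Overstatement is the more plausible direction because immobilization is the default. In the validation study, paramedics also erred conservatively: 16.4% of patients had the rule conservatively misinterpreted, including 8.5% in whom neck rotation was not evaluated as the rule requires.

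A reader might infer that the form-based denominator necessarily overstates clearance. The document does not support that. The direction turns on whether patients without a form are cleared less often than those with one. Missing forms on cleared patients would push the other way, and the article gives no data on either quantity.

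Under an assumed 80% capture and 40% clearance on forms, the overstatement is 8 points if no patient without a form is cleared and 4 points if 20% are. It is zero at 40%, and at 60% it becomes a 4-point understatement. With near-complete capture the issue is negligible. The form-based proportion remains valid as clearance when the rule is applied and documented.

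**What to change.** 1. Keep the form-based proportion, labelled as clearance among patients in whom the rule was applied and documented.
2. Prespecify, and report beside it with a 95% confidence interval, the proportion not immobilized among all eligible patients found in the census-log review. For patients without a form, take immobilization status from the ambulance call report.
3. Show patients attended by non-participating paramedics separately, and state that eligibility by mechanism alone may be incompletely captured from records.
4. Use the all-eligible figure for service-wide statements and for Phase IV planning.
5. Align the denominator wording in the outcome section and the Data analysis section, so that each names the population it covers.

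The cost is one extra field abstracted from records already opened to determine eligibility, some uncertainty over eligibility by mechanism alone, and probably a lower figure beside the headline one.

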#### Performance of the Canadian C-Spine Rule

a) Accuracy of the rule: The classification performance of the rule for clinically important cervical spine injury will be assessed with 95% CIs for sensitivity, specificity, negative predictive value, and positive predictive value. The 'criterion interpretation' of the rule, i.e. positive or negative for cervical spine injury, will be made by the investigators based on the status of the patient for the component variables as documented by the paramedic.

b) Paramedic accuracy in overall interpretation of the rule: will be calculated as the simple agreement between the paramedics' responses on the data collection form to the investigators' 'criterion interpretation' of the rule.

c) Paramedic agreement and comfort with and use of the rule: these data for each individual patient will be tabulated in a simple descriptive format.

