### Validation of the CCR by paramedics

The validation of the CCR by paramedics took place between 2002 and 2006 in seven EMS systems distributed in three Canadian provinces [77]. The study population consisted of consecutive alert, stable, and cooperative adults transported by ambulance to the local lead trauma hospital after sustaining acute blunt trauma with potential injury to the neck. These are patients for whom standard basic trauma life support (BTLS) protocols require immobilization. Patient assessment was made by primary care or advanced care paramedics, who were trained by means of a 2-hour web-based training session followed by a practical demonstration to assess the CCR and the component clinical variables in a uniform manner. The paramedics recorded their findings along with their interpretation of the decision rule itself on a data collection form prior to arrival at hospital. They followed standard procedures for immobilization of patients and did not use the CCR as the basis for the decision to immobilize. The primary outcome, acute cervical spine injury, was defined as any fracture, dislocation, or ligamentous instability demonstrated on radiography. A clinically important cervical spine injury was defined as any injury requiring internal fixation or treatment with a halo, brace, or rigid collar. All enrolled patients who did not have radiography received telephone follow-up and were classified as having no acute cervical spine injury if they met all the previously validated explicit criteria at 14 days [78].

We enrolled 2,393 eligible patients in the study. 1,126 patients were not evaluated with radiography, and required telephone follow-up. We reached 788 (70.0%) of those patients, among which 682 were determined to not have sustained a cervical spine injury according to our validated proxy assessment tool. A total of 1,949 enrolled patients had complete outcome assessments. Twelve (0.6%) had a clinically important cervical-spine injury. In two cases, the investigators could perform an independent assessment of the rule based on the paramedic care report, but could not evaluate the paramedic assessment of the rule based on their study data collection sheet. The characteristics of the 444 patients without outcome assessments were similar to those with radiographic evaluation, but were less likely to be admitted to the hospital.

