Paramedics conservatively misinterpreted the rule in 320 patients (16.4%), including 154 cases (7.9%) where "dangerous mechanism" was overcalled and 166 cases (8.5%) where paramedics did not evaluate neck rotation as required by the CCR. The CCR assessment for these patients was later categorized by the investigators as "indeterminate". Patient characteristics for these 320 patients where similar to those for which the rule was followed accurately, with the exception that none of the 320 patients had a cervical-spine injury. Paramedics did not attempt to evaluate neck rotation in any of the 12 patients with a clinically important injury. Excluding the indeterminate cases, the results yield a calculated sensitivity of 100% (95% CI 74-100%) and a specificity of 38% (95% CI 36-40). We performed secondary analyses involving all 1,949 patients to determine the potential effect of indeterminate cases when the rule was assessed by paramedics. When the rule was assumed to be positive for all indeterminate cases, the specificity was 32.4% (95% CI, 31 to 34), and when the rule was assumed to be negative for all indeterminate cases, the specificity was 46.6% (95% CI, 45 to 49). The sensitivity and negative predictive value remained the same since there were no cervical spine injuries among the indeterminate cases.

We assessed the reliability of paramedic interpretation of the rule among 155 paramedics by measuring the kappa coefficient for interobserver agreement for each element of the rule. The kappa value for the overall interpretation of the rule was 0.93 (95% CI, 0.87 to 0.99). In addition, agreement for the 8 individual components of the CCR was also very good, with kappa values ranging from 0.66 to 1.00.

The paramedics were asked to indicate on a five-point Likert scale how comfortable they would be in applying the CCR to this patient. The results were very supportive: Paramedics were "very uncomfortable" or "uncomfortable" applying the Canadian C-Spine Rule in 9.5% of cases; they were "comfortable" or "very comfortable" in 81.7% of cases.

We evaluated the potential impact of the rule on the number of necessary immobilizations. If paramedics were allowed to use the rule, 62.2% (95% CI, 60 to 64) of recruited patients would have required immobilization compared to the actual immobilization rate of 100%.

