#### Measures of safety (primary study outcomes)

a) Number of missed cervical spine injuries, i.e. number of clinically important c-spine injuries (as defined previously) identified in patients who have had their c-spine cleared by paramedics. We will know the presence of fracture or cervical spine injury from review of diagnostic imaging reports in the patient record. We also propose to institute a strategy of surveillance to identify the uncommon occurrence of a fracture missed because no radiography was ordered. ED Patient Visit Logs at each receiving hospitals will be monitored for 30 days to identify return visits by patients who do not undergo radiography during their initial ED visit. In addition, we will review the Neurosurgery Patient Logs at our regional neurosurgical centre (The Ottawa Hospital, Civic Campus). This centre provides care for patients with spinal cord injuries for the whole Ottawa region. We recognize that there is a very small risk of not identifying a missed fracture but feel that this approach is pragmatic and feasible.

b) Number of serious adverse outcomes, i.e. development of neurological deficit after c-spine clearance by the paramedics. This very unlikely subset of missed cervical spine injury cases will be determined from review of the patient records. We will monitor for the extremely rare occurrence of motor weakness and disability that develops after paramedic assessment but do not expect this to occur.

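### Paramedic accuracy is calculated only as simple agreement, which pools the two directions of error and gives no rate at which rule-positive patients are read as not needing immobilization

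*Protocol article*

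**What the plan says.** In the protocol article, Data analysis, Performance of the Canadian C-Spine Rule, item b), paramedic accuracy "will be calculated as the simple agreement between the" paramedic's answer on the form and the investigators' criterion reading. No other statistic is named for it. The comparison is binary: immobilization needed or not needed.

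Four other places bear on the point:

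- **Secondary outcomes, item b).** The definition of this same outcome adds: "Attention will be focused on fractures missed or potentially missed by paramedic misinterpretation".
- **Data analysis, same heading, item a).** Sensitivity, specificity and predictive values are calculated for the investigators' criterion reading, which is built from the component variables that the paramedic recorded. They are not calculated for the paramedic's own reading.
- **Measures of safety (primary study outcomes), item a).** Missed injuries are the "number of clinically important c-spine injuries (as defined previously) identified in patients who have had their c-spine cleared by paramedics". The analysis section lists these cases and gives a percentage with a 95% CI.
- **Validation of the CCR by paramedics.** The earlier study reported 320 conservative misinterpretations (16.4%): 154 with an overcalled dangerous mechanism and 166 with neck rotation not evaluated. The investigators later classed all 320 as indeterminate.

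**The concern.** The two ways of disagreeing with the criterion have different consequences. If a rule-positive patient is read as not needing immobilization, protection may be withheld from someone the rule would protect. If a rule-negative patient is read as needing it, the result may be an unnecessary immobilization, with the discomfort and delay that the Background describes, and a smaller clinical impact. Simple agreement counts both equally and reports their sum.

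Item b) is the only planned calculation that sets the paramedic's own reading against the rule. If it stays undirected, the plan as written yields no estimate of how often paramedics turn a positive rule into a clearance. In the validation study it was the direction of the 16.4% that made it reassuring, and the planned figure would not carry that information.

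**Working it through.** **Inputs (all from the protocol article)**

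- Planned enrolment 3,000; expected clinically important injuries 20 (Sample size).
- Validation study: 1,949 patients with complete outcomes; 12 clinically important injuries; 320 conservative misinterpretations; 62.2% would have required immobilization (Validation of the CCR by paramedics).

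**Step 1. Reproduce the stated figures.** 320/1,949 = 16.4%; 154/1,949 = 7.9%; 166/1,949 = 8.5%. All match. Expected injuries: 3,000 × 12/1,949 = 18.5, consistent with the stated 20.

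**Step 2. Hold agreement fixed and vary direction.** Agreement = 1 − (unsafe + conservative)/N. Rule-positive: 0.622 × 3,000 = 1,866. Rule-negative: 1,134. Disagreements: 3,000 × 320/1,949 ≈ 493. The share of disagreements that is unsafe is an assumption.

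| Assumed unsafe share | Rule-positive read as clear | As % of 1,866 | Agreement |
|---|---|---|---|
| 0% | 0 | 0% | 83.6% |
| 10% | 49 | 2.6% | 83.6% |
| 50% | 246 | 13.2% | 83.6% |
| 100% | 493 | 26.4% | 83.6% |

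**Step 3. Sensitivity to the rule-positive share.** The 62.2% appears to go with the 38% specificity, which excludes the indeterminate cases, whereas 16.4% uses all 1,949. The two specificities given for all 1,949 patients allow a common denominator. Patients without injury number 1,949 − 12 = 1,937.

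- Indeterminate taken as positive (specificity 32.4%): rule-negative 0.324 × 1,937 ≈ 628; rule-positive share 1 − 628/1,949 = 67.8%; ceiling 16.4/67.8 = 24.2%.
- Indeterminate taken as negative (specificity 46.6%): rule-negative 0.466 × 1,937 ≈ 903; rule-positive share 1 − 903/1,949 = 53.7%; ceiling 16.4/53.7 = 30.5%.

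The ceiling moves between about 24% and 31%. The floor stays at 0%, and agreement stays at 83.6%.

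**Step 4. Would kappa help?** With 62% rule-positive and 16.4% disagreement, kappa = (agreement − chance)/(1 − chance).

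- All conservative: paramedic-positive share 0.62 + 0.164 = 0.784; chance 0.62 × 0.784 + 0.38 × 0.216 = 0.568; kappa (0.836 − 0.568)/(1 − 0.568) = 0.62.
- Half unsafe: paramedic-positive share 0.62; chance 0.62² + 0.38² = 0.529; kappa (0.836 − 0.529)/(1 − 0.529) = 0.65.

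Kappa is slightly better in the less safe case, so adding it would not close the gap.

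**Step 5. Do the injury-based provisions cover it?** Suppose all 20 injured patients are rule-positive, misreading is unrelated to injury, and every misread patient is cleared. With 2.6% of rule-positive patients misread, the chance of no missed injury is 0.974^20 ≈ 59%. With 5% it is 0.95^20 ≈ 36%. A clean injury count is therefore compatible with appreciable misreading.

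**The case against.** The strongest reply is that safety is assigned elsewhere. Paramedic accuracy is secondary; missed injuries and neurological deficit after clearance are primary. A wrongly cleared patient with an identified injury is counted there, whether the rule or its reading failed. This stands. A reader might infer that the study cannot show safety because of this statistic, and the documents do not support that.

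Other stronger readings also fail:

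- **That the plan ignores direction.** The outcome definition singles out fractures missed or potentially missed through misinterpretation. This is case-level and gives no rate, but it is there.
- **That conservative errors are harmless.** The section Cervical spine immobilization describes restricted breathing, worsening pain and extra radiography.
- **That hundreds of patients would be wrongly cleared.** The 16.4% counts conservative misreadings later classed as indeterminate; it is not a total disagreement rate. No document figure supports any unsafe share. A form response is also not the same as management, since paramedics may override the rule.
- **That the unsafe-misreading rate would be the best-powered safety signal.** Zero in 1,866 would give an upper 95% limit of 1 − 0.025^(1/1,866) = 0.20%. But the criterion uses findings that the paramedic recorded, so this bounds errors in applying the rule to those findings. It cannot detect findings recorded wrongly. It is a process measure.

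It can also be said that a cross-tabulation is reporting detail left to a fuller document. That would answer a silence. Here the article names the statistic, and the one it names cannot show direction. Still, nothing forbids the breakdown, and the same group reported direction before.

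**Conclusion.** The point holds as a limited one about a secondary outcome. The only calculated comparison of the paramedic's reading with the rule is undirected, and no other planned analysis gives a rate of rule-positive patients read as clear. At 83.6% agreement that rate could be anywhere from 0% to about 26% (24% to 31% at the ceiling, depending on how indeterminate cases enter the denominator). This range shows what the statistic cannot distinguish; it is not a forecast. It rests on borrowing the validation study's 16.4% as total disagreement and on an assumed split by direction. The primary safety outcome is unaffected. The change is worth making because the two readings it needs are already planned.

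**What to change.** In Data analysis, Performance of the Canadian C-Spine Rule, item b), replace the single agreement figure with the paramedic-by-criterion table, keeping indeterminate readings as their own category. Report with 95% CIs:

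1. the proportion of criterion-positive patients whom the paramedic read as not needing immobilization;
2. the proportion of criterion-negative patients whom the paramedic read as needing it.

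Keep overall agreement beside these. Add sensitivity and specificity for clinically important injury based on the paramedic's own reading, next to those already planned for the criterion reading. State that the criterion relies on components recorded by the paramedic, so the two rates measure errors in applying the rule to recorded findings and do not replace the primary safety outcome.

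Cost: a few sentences and a small amount of extra analysis, with no new data collection. The handling of indeterminate cases must be stated in advance, because forcing them into either column would shift both rates.
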